# Effects of transcranial direct current stimulation on gait in people with Parkinson’s disease: study protocol for a randomized, controlled clinical trial

**DOI:** 10.1186/s13063-018-2982-z

**Published:** 2018-11-29

**Keywords:** Parkinson’s disease, Transcranial direct current stimulation, Gait

## Abstract

**Background:**

Gait difficulties are common and frequently devastating to people with Parkinson’s disease (PD). These difficulties are often followed by an increased risk of falls, leading to injury, hospitalization and mortality. The dysfunction in the basal ganglia-thalamocortical motor circuits and reduced activity in the premotor and primary motor cortices has raised interest in transcranial direct current stimulation (tDCS) as an adjunct intervention in PD. tDCS might provide a potentially safe and non-invasive treatment by modulating cortical excitability and behavioural outcomes. The aim of this study is to compare the effects of different monopolar and bipolar montages of tDCS administered to the motor cortex and cerebellum on gait speed in PD.

**Methods:**

This study will be conducted in a randomized, double-blind cross-over design. Eighteen participants diagnosed with Parkinson’s disease will receive anodal and sham tDCS (1 mA, 20 min, 10 × 4 cm^2^) over the premotor and primary motor cortices with the cathode over the cerebellum during treadmill walking. Three montages will be applied over three sessions and compared: anodal tDCS with a small active cathode (4 × 4 cm^2^); anodal tDCS with a large, functionally inert cathode (10 × 10 cm^2^); and sham tDCS. The primary outcome measure is gait speed, and secondary outcome measures include gait parameters (temporospatial, segmental, kinematic), the Timed Up and Go test and lower limb muscle activity patterns as measured by electromyography.

**Discussion:**

This study will investigate the short-term effects of anodal tDCS over the premotor and primary motor cortices on gait abilities using monopolar and bipolar montages in people with PD. The outcomes will inform future studies aimed at inducing longer-lasting changes in neural excitability and performance using multisession tDCS designs in PD.

**Trial registration:**

Australian New Zealand Clinical Trials Registry (ANZCTR), ACTRN12618000063213. Registered on 17 January 2018. Retrospectively registered.

**Electronic supplementary material:**

The online version of this article (10.1186/s13063-018-2982-z) contains supplementary material, which is available to authorized users.

## Background

Gait difficulties are common and often incapacitating for individuals with Parkinson’s disease (PD). They manifest as reduced gait speed, stride length, coordination and arm swing [1] as well as increased cadence, upper body movement and double support duration [2, 3]. Underpinning this altered gait are changes in muscle activation. This includes increased activation of hamstrings and quadriceps in mid-stance and late stance phases and decreased activation of tibialis anterior and gastrocnemius lateralis muscles in early stance phase, which results in delayed heel-off phase and gait initiation [4, 5]. Importantly, gait deficiencies result in a nine-times greater risk of falls [6], leading to a five-times greater risk of sustaining fall-related injuries, hospitalization and mortality for people with PD [3].

Motor complications in PD have been linked to degeneration of dopaminergic neurons in the substantia nigra compacta of the basal ganglia, which results in a deficit of dopamine and disruption of dopaminergic neurotransmission [7]. There is a consequent dysfunction in the basal ganglia-thalamocortical motor circuits with an overactivity of inhibitory efferents from the basal ganglia to the thalamus, resulting in suppression on thalamocortical projections, with abnormal activity in the premotor and primary motor cortices, resulting in gait difficulties [8, 9]. The dopamine deficit and dysfunction in the basal ganglia-thalamocortical motor circuits also affect cortico-cerebellar circuits as they are functionally connected [10, 11]. The cerebellum has been shown to be hyperactive in PD, presumably to compensate for the deficiency in function of the basal ganglia and the cortico-cerebellar circuit [10].

Non-invasive brain stimulation of the premotor and primary motor cortices may modulate neural activity in these neural circuits [10, 12, 13] and re-equilibrate the cortico-cerebellar circuits [14], thereby improving gait ability and lower limb muscle activity in people with PD.

Transcranial direct current stimulation (tDCS) is a non-invasive brain stimulation technique now widely used in neuroscience and clinical research in humans [15, 16]. It has an excellent safety profile [17] and is a low-cost technique suited for double-blind clinical trials [18]. The tDCS process modulates cortical excitability via a weak direct current that is delivered by two or more scalp-affixed electrodes [19]. Anodal tDCS (a-tDCS) typically increases cortical excitability and cathodal tDCS (c-tDCS) decreases it [13]. The underlying mechanisms by which tDCS modulates neurophysiology and behaviour are yet to be fully understood [20]. However, acute effects of a single session (e.g. 20–30 min) might result in transient modulation of the neural resting membrane potential [19, 21]. Further, the cumulative effects of repeated tDCS sessions can be explained by modulation of post-synaptic connections, similar to long-term potentiation and long-term depression, which play a key role in neuroplasticity underlying adaptive human behaviour and learning [19].

Emerging research suggests the potential for a-tDCS over the primary motor cortex (M1) to improve gait difficulties in PD due to the dense connectivity of the cortex and the basal ganglia, and the possibility of targeting the basal ganglia-thalamocortical motor circuits [22–27]. However, results from previous studies have indicated that the effects of tDCS on gait speed [24, 26–34] and stride length [24, 27, 32] have been variable and appear to be dependent on stimulation site and electrode size. In one study, bilateral a-tDCS (3.5 × 5 cm^2^) of either premotor and motor or prefrontal cortices with the cathode (5 × 5 cm^2^) over the mastoid demonstrated significant improvement in gait speed [28]. The most substantial gait improvement was reported by Kaski et al. (2014) after applying bilateral a-tDCS combined with physical training or tango [33, 35]. This bilateral arrangement was employed because gait control is the result of parallel and bilateral involvement of motor and premotor cortices; the authors used a bilateral stimulation set-up, and the anode (10 × 4 cm^2^) was centred over the premotor and primary motor cortices. The cathode (4 × 4 cm^2^) was attached over the inion to ensure current flow through the sensorimotor strip but without affecting the cerebellum. While this montage showed beneficial effects on gait speed and stride length, it remained unclear whether these effects were mediated by sensorimotor effects of the anode, possible inhibitory effects on the cerebellum due to the proximity of the cathode to this region or synergetic effects induced by the bipolar set-up. Therefore, a systematic investigation of electrode size and placement, which most likely determine the extent of tDCS effects on gait abilities in PD, is required.

In the present study, we will address this issue by systematically investigating the effects of a-tDCS over the premotor and primary motor cortices and the synergetic effects of a-tDCS over the premotor and primary motor cortices and c-tDCS over the cerebellum. As it is thought that tDCS is most effective when combined with a behavioural task [36], tDCS will be administered during simultaneous treadmill walking, because a recent study reported more pronounced effects after this task compared to other physical tasks in PD [37]. This ensures that the neural circuits, and particularly M1, are active during application of the tDCS. In this study, we also took advantage of the same anode electrode parameters used in studies by Kaski et al. [30, 33, 35, 38]. Applying bilateral a-tDCS over the premotor and primary motor cortices and comparing the effects of both active (small) and functionally inert (large) cathodes over the cerebellum in PD could disentangle the location of possible tDCS effects on gait abilities in PD. We hypothesize that a large cathode will render stimulation over the cerebellum inactive (i.e. a monopolar M1 set-up), whereas a smaller cathode will exert additional inhibitory effects on the cerebellum (i.e. a bipolar M1 cerebellar set-up) [39]. To our knowledge, no study to date has analysed the gait parameters and electromyography (EMG) of the lower limb focusing specifically on different bilateral tDCS montages.

Thus, this randomized placebo (“sham tDCS)” controlled study aims to examine the short-term effects of (1) monopolar bilateral a-tDCS over the premotor and primary motor cortices (exploratory aim 1); (2) bipolar bilateral a-tDCS over the premotor and primary motor cortices and cerebellum cortex (exploratory aim 2) while walking on a treadmill on gait speed as the main outcome measure and other gait kinematics and EMG in people with PD when optimally medicated. The findings will be reported and disseminated through peer-reviewed journal publication and conference presentations. The results of the study will also be presented for PD support groups who contributed in participant recruitment.

## Methods

### Study design and outline

The study will employ a randomized, double-blind, sham-controlled cross-over design to assess the effect of a-tDCS delivered during treadmill walking on natural overground gait performance and associated muscle activation. Participants will receive bilateral active or sham tDCS for 20 min while walking on a treadmill over three sessions. Gait will be assessed using a three-dimensional (3D) motion capture system and EMG before and after applying tDCS in each session. All assessment will be conducted by the principal researcher, who was trained for conducting all the assessments. The overall study design is illustrated in Fig. 1. A Standard Protocol Items: Recommendations for Interventional Trials (SPIRIT) schedule is presented in Fig. 2, and a SPIRIT checklist is available in Additional file 1. The steering committee is the supervisory panel for the principal researcher, and data monitoring is done by the Research Method Advisory Group in the Institute of Health and Biomedical Innovation (IHBI) at Queensland University of Technology (QUT). The trial will be monitored on a weekly basis by the supervisory panel. The Institutional Human Research Ethics Committee approved the research. The ethics committee will be informed of any trial modifications, and these updates will be made to the trial information on the Australian New Zealand Clinical Trials Registry website. The study will be undertaken and reported based on the Consolidated Standards of Reporting Trials (CONSORT) statement for non-pharmacological treatment.

**Fig. 1 Fig1:**
[figure not shown]
Flowchart of overall study design. Note: Active tDCS is either monopolar bilateral a-tDCS over premotor cortex and primary motor cortex or bipolar bilateral a-tDCS over premotor cortex, primary motor cortex and cerebellum cortex

**Fig. 2 Fig2:**
[figure not shown]
SPIRIT schedule

### Participants

Eighteen participants diagnosed with idiopathic PD aged 40–80 years old will be recruited from (1) Parkinson’s Queensland Incorporated (PQI), i.e. a community-based PD advocacy and support group; (2) local neurology clinics; (3) PD support groups; (4) advertisement via university website, emails and Facebook. Potential participants will be sent an information sheet explaining the details of the study and an invitation to contact one of the research team members if they wish to participate in the study.

Interested participants will initially be screened for the basic exclusion criteria, contraindications and special considerations before tDCS via a telephone screening procedure. Exclusion criteria will compromise the presence of the following: uncorrected vision impairment, heart failure, uncontrolled blood pressure, cardiovascular disease, asthma, vertigo, frequent falls, dizziness, musculoskeletal injuries within the last 18 months and orthopedic surgery within the last 12 months. The tDCS exclusion criteria include having a previous adverse reaction to transcranial magnetic stimulation (TMS)/tDCS, seizure, unexplained loss of consciousness, stroke, serious head injury, surgery to the head, any brain-related neurological illness other than PD, any illness that may have caused brain injury, frequent or severe headache, having any metal in the head, having any implanted medical device, being pregnant and having any epileptic family members. Participants meeting basic inclusion criteria for participation in the study will be scheduled to visit the movement assessment laboratory, provided with full participant information by the principal researcher on the nature of the study and asked to provide written informed consent. They will undergo a clinical eligibility screening as well as baseline clinical assessments at the IHBI, QUT. For testing at the IHBI, emergency procedures will be followed as per QUT policy. QUT provides for limited counselling services (face-to-face only) for research participants of QUT projects who may experience discomfort or distress as a result of their participation in the research. Once recruited into the study, participants will be sent reminders via emails and text messages to ensure adherence to attending the three testing sessions. Participants will be asked not to start a new intervention until they complete the trial. However, if they wish to, they will be permitted to do so, and any new intervention will be documented.

### Clinical eligibility screening

Clinical assessments will test (1) cognitive function using Addenbrooke’s Cognitive Examination Revised (ACE-R), whereby a score < 82 indicates likely dementia [40]; (2) disease severity using the Movement Disorder Society Unified Parkinson’s Disease Rating Scale (MDS-UPDRS), where the total UPDRS score is determined as the sum of the scores of all items. Each item can be rated with scores of 0 = normal to 4 = severe; the higher the total score, the more severe the disease [41].

### Clinical baseline assessment

Eligible participants will be asked to perform further clinical assessments, including:Visual function including contrast sensitivity and visual acuity. Contrast sensitivity will be assessed using the Pelli-Robson chart with normal values of 1.80–2.10 at both 1 and 3 m distance for persons 40–59 years old, and 1.65–1.95 at 1 m and 1.65–2.10 at 3 m for those ≥60 years old [42] ; and the Melbourne Edge Test, where abnormal values differ for different age groups ranging from < 22 in individuals younger than 50 years to < 14 in individuals older than 80 years old [43]. Visual acuity will be assessed using the Bailey-Lovie chart set, where the values of the logarithm of the minimum angle of resolution (logMAR) range from normal (− 0.3) to poor (1.00) [44, 45].Lower limb peripheral sensation (internal and external malleolus, distal phalanx of third toe, arch of foot, heel and dorsum of proximal phalanx of toe) will be assessed using a Semmes-Weinstein-type pressure aesthesiometer; the lower tactile threshold score, the better [46].Mobility will be assessed using the Tinetti balance and gait test, whereby a value ≤18 suggests high risk for falls and ≥ 24 suggests low risk for falls [47].

Following the clinical assessments, questionnaires will be provided to the participants to be completed at their convenience at home, including demographic information, the International Physical Activity Questionnaire (IPAQ) [48], the Activities-specific Balance Confidence (ABC) Scale [49], a medication diary to calculate levodopa equivalent daily dose, quality of life questionnaires (Parkinson’s Disease Questionnaire (PDQ-39) [50], Parkinson’s diseases gait and falls questionnaire [51] and the UPDRS (Part 2: activities of daily living; patient questionnaire section) [52]. All questionnaires have good psychometric properties and have been used in previous PD trials [3].The participants will be asked to attend the gait laboratory for three visits with at least a 1-week interval between them and to return the completed questionnaires on the first visit. The assessments and the time points and all outcome measures at which the assessments will be taken are presented in Table 1. All questionnares and forms will be found in the online thesis, which will be available via the QUT library.

**Table 1 Tab1:** Baseline and follow-up outcome measures

Outcome measure	Instrument	To be completed at convenient time	Visit 1		Visits 2–4
			Screening	Clinical	
Clinical/screening measures					
Cognitive function	Addenbrooke’s Cognitive Examination (ACE-R)		✓		
Disease severity	Unified Parkinson’s Disease Rating Scale (UPDRS) and Hoehn and Yahr scale		✓		
Visual function					
Visual acuity	Binocular visual acuity: Bailey-Lovie			✓	
Contrast sensitivity	Pelli-Robson contrast sensitivity chart			✓	
	Melbourne Edge Test			✓	
Touch sensitivity	Semmes-Weinstein monofilament test			✓	
Clinical balance and gait	Tinetti Gait and Balance Instrument				✓
Mobility	Timed Up and Go (TUG) test				✓
Gait characteristics					
Spatiotemporal parameters	Nexus 2.6; Vicon, Oxford, UK				
Gait speed (m/s)					✓
Cadence (step/min)					✓
Spatial parameters (cm)	Nexus 2.6; Vicon, Oxford, UK				
Stride length					✓
Step length					✓
Step width					✓
Maximum toe clearance					✓
Temporal parameters (s and % GC)	Nexus 2.6; Vicon, Oxford, UK				
Stride/stance/swing/single support/double support/GC time					✓
Segmental linear motion (cm)	Nexus 2.6; Vicon, Oxford, UK				
Centre of mass (COM) VT/ML					✓
Head displacement, VT/ML					✓
Pelvis displacement, VT/ML					✓
Arm swing excursion					✓
Joint kinematics (deg)	Nexus 2.6; Vicon, Oxford, UK				
Trunk flexion angle					✓
Hip flexion/extension range					✓
Knee flexion/extension range					✓
Ankle dorsiflexion/plantar flexion range					✓
Joint angles (hip, knee, ankle) of stance and swing leg at maximum toe clearance					✓
Muscles activity (per muscle)	ZeroWire, Aurion Srl, Milan, Italy				
EMG onset and offset time					✓
Duration of muscle activity					✓
Total burst activation (integral of rectified EMG)					✓
Time of peak muscle activation					✓
Questionnaires					
Balance confidence	Activities-specific Balance Confidence (ABC) Scale	✓			
Freezing of gait (FOG) and falls	PD gait and falls questionnaire (FOG section)	✓			
Physical activity	International Physical Activity Questionnaire (IPAQ)	✓			
Quality of life	The 39-item Parkinson’s Disease Questionnaire (PDQ-39)	✓			

*AP* anteroposterior, *EMG* electromyography, *GC* gait cycle, *ML* mediolateral, *VT* vertical

### Primary and secondary outcomes

The primary outcome will be gait speed, and secondary outcomes include other gait kinematics, muscle activation and functional mobility (Table 1).

#### Pre- and post-tDCS assessments

##### Three-dimensional gait assessment

Objective gait evaluation will be performed using a typical 3D assessment relying on motion capture [53, 54]. Gait speed as the primary outcome and all kinematic data will be collected using the Vicon system (Nexus 2.6; Vicon, Oxford, UK) including 12 cameras recording markers at 200 Hz within a calibration volume (e.g. L:9.3 × W:2.6 × H:2.5 m).

A total of 39 spherical markers (14 mm) will be positioned over body landmarks, based on a modified Helen Hayes marker set [3], including the head (forehead and back of the head); trunk (C7 spinus process, tenth thoracic vertebra, right scapula, jugular joint and xiphoid process); hips (anterior superior Iliac spine and posterior superior iliac spine); upper limbs (lateral border of acromion, upper arm, olecranon process of the humerus, lower arm, radial and ulnar styloids and second metacarpal head); and lower limbs (thigh, tibia, knee, ankle, second metatarsal head). Markers will be attached directly onto the skin using double-sided and hypafix tape. Marker placement will be performed by the same researcher in each session to minimize inter-tester variability. The 3D position of the markers will be expressed in the Global Coordinate System (GCS) placed approximately 1.3 m on the right side and 4.6 m behind the centre of the 10-m straight walkway.

First, the participant will be asked to walk naturally 10 times over the walkway to establish his/her self-selected walking speed. This speed will be used to set the treadmill speed during the tDCS sessions. Next, the participant’s anthropometrics will be measured and entered into the Vicon Nexus software, including body mass, height, leg length, knee and ankle width, elbow and wrist width and hand thickness.

Then, an initial recording of the participant standing still in the middle of the capture volume will be conducted for static calibration to facilitate automated detection and tracking of markers. Finally, the participant will be asked to walk six times in a straight line, over even and uneven surfaces on the walkway located in the middle of the calibration volume. Sufficient rest will be allowed in between trials to avoid participant’s fatigue.

##### Timed Up and Go (TUG) test

Basic functional mobility will be assessed with the TUG test, providing the time required to rise from a chair, walk 3 m at a comfortable pace, turn, return to the chair and sit down [55]. In the present study, participants will complete a practice trial first. Two trials will then be completed and recorded; the second trial will include a dual task [26]. The participants will be asked to count backwards in threes from a randomly chosen number between 60 and 100 while performing the TUG test.

##### Electromyography

Muscle activation will be recorded at 1 kHz using the surface EMG bilateral ZeroWire system (ZeroWire, Aurion Srl, Milan, Italy). Recordings will be taken from the right and left lower limb muscles involved in gait: tibialis anterior, soleus, lateral and medial head of gastrocnemius, rectus femoris, biceps femoris, semitendinosus and vastus lateralis. Prior to applying the surface electrodes on the belly of the muscles of interest, participants with excessive hair over the muscles of interest will be shaved, using single-use disposal safety razors. Then, the skin will be cleaned thoroughly with a cotton ball and alcohol. This reduces impedance at the electrode-skin interface and improves the clarity of the myoelectric signal. After the skin is prepared, two Ambu surface electrodes (size 8 × 22/30 × 22; electrode diameter 30 × 20; inter-electrode distance 25 mm) will be placed on the muscles of interest according to the European recommendations for surface electromyography, Surface EMG for the Non-Invasive Assessment of Muscles (SENIAM) [56]. Muscle palpation will also be done to ensure validity of electrodes placement due to the anatomical variations between individuals.

### Intervention (a-tDCS and sham tDCS) during treadmill walking

The tDCS will be delivered using a portable battery-driven NeuroConn DC Plus stimulator. To ensure that the DC stimulator is not dropped, it is placed on the treadmill panel in front of the participant. Each participant will undergo two active a-tDCS sessions and one sham tDCS session with at least 1 week interval so that we avoid carry-over effects. The washout period in studies into PD and tDCS is varied between 48 h [57] to 1 week. The results of the statistical analysis for testing carry-over effects did not show any of these effects [57]. Therefore, a 1-week interval will be an appropriate washout period.

The anode will be placed centrally over the motor strip to cover a region 10–20% anterior to Cz during treadmill walking in all three sessions. To manage the risk of falls, participants will wear a harness if required. The position and size of the anode proposed in this study have been used by Kaski et al. [30, 33, 38] in a series of studies with positive effects on gait speed [30, 33, 38]. The cathode (either 10 × 10 or 4 × 4 cm^2^) will be placed over the cerebellum, 2 cm below the inion on the median line, over the three sessions. The cathode placement in the two active tDCS sessions will be counterbalanced across the participants. Thus, one third of the participants will receive active tDCS with a large cathode first, and another one third of the participants will receive active tDCS with a small cathode electrode first; the final third of the participants will receive sham tDCS with either a small or large cathode electrode (50% each). Electrodes will be inserted in saline-soaked sponge pockets. A cap and a strap will be used to attach the electrodes over the target locations. The current will be ramped up to 1 mA over 10 s in the active stimulation conditions and held constant for 20 min before ramping down over 10 s at the end of the stimulation [18]. In the sham condition, the current will be ramped up and down, at the beginning and at the end of the 20-min tDCS session (i.e. no active stimulation is administered in between). During both stimulation conditions (active and sham) all participants are asked to walk on a level Nautilus treadmill, and they will be allowed to use the hand rails. The principal researcher will apply the tDCS electrodes and oversee all aspects of the experiment. The tDCS will be terminated immediately if the participants become uncomfortable with it. The severity of adverse effects will be assessed using a scale suggested by Brunoni et al. [58] after each tDCS session.

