#### Blinding and randomization

Blinding of the principal researcher will be achieved by using the “study mode” of the DC stimulator. The study mode activates active and sham stimulation with digital codes. To minimize biasing the outcomes, an independent researcher creates a list of participants using block randomization. A randomization sequence is produced through random permutations generated by a stochastic process program in R software version 3.3.4. The size of the blocks will be set to 3 with a ratio of 1:1 so that we need six blocks of the collection (1. ABC, 2. BAC, 3. BCA, 4. CBA, 5. CAB, 6. ACB). We will draw six numbers randomly and sequentially from this collection.

In the randomization list the preprogrammed digital codes of tDCS and the size of the cathode electrode will be assigned to each participant for each session and submitted to the principal researcher via a sealed envelope. The independent researcher provides the digital code and cathode electrode size for the principal researcher prior to each tDCS session. The DC stimulator display continues to indicate the impedance and the time in the same fashion for both active and sham tDCS. The principal investigator will be blinded to the participant and experimental condition during the processing and analysing of the gait data. However, in the case of an adverse event, where it is necessary for the principal researcher to know which stimulation the participant is receiving, the principal researcher will be unblinded. Data from the identifiers will be removed and replaced by codes. However, the data will be re-identifiable by using the code or linking the participant’s details to their allocation and to their different datasets. Reliability of blinding will also be assessed after each tDCS session by asking participants about the type of stimulation they believed they had received [58]. The principal investigator will also guess and record which stimulation type the participant had received.

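### The trial is called double-blind, but the assessor knows the cathode size: small versus large cathode is not masked from the assessor, and active versus sham is only partly masked

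*Protocol article*

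**What the plan says.** Under Study design and outline, the protocol article states: "The study will employ a randomized, double-blind, sham-controlled cross-over design". The same section gives outcome assessment to one person: "All assessment will be conducted by the principal researcher".

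Under Intervention, that person also handles the electrodes: "The principal researcher will apply the tDCS electrodes and oversee all aspects of the experiment". Each participant has three sessions: "Each participant will undergo two active a-tDCS sessions and one sham tDCS session". The cathode is either 10 × 10 or 4 × 4 cm and "will be placed over the cerebellum, 2 cm below the inion on the median line, over the three sessions". On sham, the section says that "the final third of the participants will receive sham tDCS with either a small or large cathode electrode (50% each").

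Under Blinding and randomization, the device that masks the principal researcher is the stimulator's study mode, which uses digital codes for active and sham stimulation. The cathode size is disclosed: "The independent researcher provides the digital code and cathode electrode size for the principal researcher prior to each tDCS session". The section also says that the principal investigator will be blinded to participant and condition while gait data are processed and analysed, that identifiers are replaced by re-identifiable codes, and that participants and the principal investigator each record a guess of the stimulation type.

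Gait data processing has heel-contact and toe-off detected manually. EMG data processing assigns the gait and EMG processing to the principal researcher.

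**The concern.** Study mode hides whether current flows. It cannot hide which of two very different pads (16 versus 100 cm²) is being strapped on, and the person strapping it on runs the tests before and after stimulation. The article describes no way of concealing the size, no separate person to apply electrodes and no independent assessor.

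The comparison of the monopolar and bipolar montages is a main purpose of the trial, according to the Abstract, Background and Discussion, and cathode size is what separates them. Gait speed is measured during natural overground walking and the TUG test at a comfortable pace, so both can respond to how the assessor instructs or encourages the participant. A reader who takes double-blind at face value would give the montage contrast more protection against this than the procedures provide. The investigator's recorded guesses are affected too, because cathode size informs them.

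**Working it through.** The plan gives no figure on this point to reproduce, so the check is a complete enumeration.

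**Inputs.** Three conditions per participant: active with large cathode (AL), active with small cathode (AS) and sham (SH), from the Abstract and Intervention. Sham uses size L or S, 50% each (Intervention). All six orders are possible (Blinding and randomization) and are taken as equally likely. This gives 6 × 2 = 12 arrangements.

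| Order | Sizes if sham is L | Once-only size | Sizes if sham is S | Once-only size |
|---|---|---|---|---|
| AL, AS, SH | L S L | session 2, AS | L S S | session 1, AL |
| AL, SH, AS | L L S | session 3, AS | L S S | session 1, AL |
| AS, AL, SH | S L L | session 1, AS | S L S | session 2, AL |
| AS, SH, AL | S L L | session 1, AS | S S L | session 3, AL |
| SH, AL, AS | L L S | session 3, AS | S L S | session 2, AL |
| SH, AS, AL | L S L | session 2, AS | S S L | session 3, AL |

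**Step 1: what size reveals at a single session.** A small cathode excludes AL and a large one excludes AS. Naming the active condition of the size seen is correct whenever the session is active, which is 2 sessions in 3. The chance of naming the condition therefore rises from 1/3 to 2/3. At session 1, P(sham given size) = (1/3 × 1/2) / (1/3 + 1/3 × 1/2) = (1/6)/(1/2) = 1/3, the same as with no size information.

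**Step 2: the once-only size.** In 12 of 12 arrangements one size occurs exactly once, and that session is active. This needs no 50% split: each participant has one active session of each size, and sham repeats one of them.

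**Step 3: when this becomes known.** The once-only size falls in session 1, 2 or 3 in 4 of 12 arrangements each.
- Session 3 (4/12 = 1/3; sizes L L S or S S L): two equal sizes have already been seen, so the different third size is known to be active before that session's post-test. With 18 participants, 18 × 1/3 = 6 are expected.
- Session 1 or 2 (8/12 = 2/3): the proof comes only when the session 3 size is given, after the once-only session has been assessed.

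**Step 4: what stays masked.** At session 2, P(sham) is 1/4 if the size differs from session 1 and 1/2 if it is the same. Once all three sizes are known, the two same-size sessions remain 50/50. The chance of naming the whole order rises from 1/6 to 1/2, because each size pattern in the table fits exactly two orders.

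**Step 5: the processing stage.** The promised blinding applies while data are processed and analysed. It cannot act on live testing. The data are processed by the person who collected them, gait events are marked by hand, and the article does not say who removes the identifiers.

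**The case against.** A fair defence has several parts.

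- **Size is not the condition.** The Abstract says "Three montages will be applied over three sessions and compared: anodal tDCS with a small active cathode", then lists the large-cathode version and sham. A reader might infer that the assessor knows the condition at every session. The documents do not support that: sham uses either size, and the chance of a correct name is 2/3. This stands.
- **Active versus sham is still largely masked.** Always guessing active is right in 2/3 of sessions, and knowing the size does not raise that average. At session 3, for example, it is 1/3 × 1 + 2/3 × 1/2 = 2/3. Size produces certainty in some participants, not a better guess overall. This stands, and it is why the masking is called incomplete and not absent.
- **Timing of release.** A reader might infer that the size is known before the pre-test, or that the sealed envelope hands over the whole list at the outset. The article uses session both for the visit and for the stimulation period, and the sentence after the envelope describes release before each session. Neither inference is established.
- **Other safeguards.** Processing-stage blinding, coding and recorded guesses are planned, and 12-camera motion capture limits measurement error by the assessor. These count, but none acts on what the assessor says or does during live testing.
- **Participants.** They wear the different cathodes, but nothing in the documents shows that they are unblinded.

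The defence does not reach the central fact that the outcome assessor knows which cathode is in place at every post-test.

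**Conclusion.** The point holds in this form. Double-blind is not accurate for the small- versus large-cathode contrast, because the assessor sees the feature that defines it at 100% of sessions. For active versus sham, assessor masking is incomplete: one session per participant can be proved active (12 of 12 arrangements), before its post-test in one third of participants and retrospectively in two thirds.

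The conclusion assumes that no undescribed concealment or second operator exists, and that the principal researcher and principal investigator are the same person. The 12-of-12 result also needs sham to use one of the two stated sizes in every participant. The 50% sentence seems to concern those who receive sham first, but no other size is mentioned. The one-third figure further assumes equally likely orders, with sham size unrelated to order. The documents give no figure for the effect of assessor behaviour on gait speed, so the resulting bias cannot be sized. The design stands; its label and the strength of the montage conclusion should be corrected.

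**What to change.** 1. Replace double-blind with a statement that participants are to be blinded, and that the assessor is masked to current on or off only, incompletely, and not to cathode size. Limit the monopolar-versus-bipolar conclusion to match.
2. State that code and cathode size are released one session at a time, after that session's pre-tDCS assessment is finished. This protects the pre-test but not the post-test. Trial status expects completion in November 2018 and the article is dated 29 November 2018, so it may help few remaining sessions.
3. Make the processing-stage blinding workable: the independent researcher who holds the list re-labels motion and EMG files by participant, session and pre/post before gait events are detected.

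The cost is wording, envelope handling and file re-labelling by someone already in the plan. The downside is a less favourable blinding claim.
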